## Abstract

Community-dwelling older adults suffer from chronic pain. Pain negatively affects their physical and psychosocial wellbeing. The majority of pain management education and programs focus only on older adults. Their informal caregivers should be involved in pain management. A dyadic pain management program for reducing pain and psychological health symptoms, and improving pain self-efficacy, quality of life, and physical function in older adults is proposed for evaluation of its effectiveness. This will be a cluster randomized controlled trial. Community-dwelling older adults aged 60 or above and their informal caregivers will be recruited. The dyadic pain management program will be an eight-week group-based program. The participants in the experimental group will receive four weeks of center-based, face-to-face activities and four weeks of digital-based activities via a WhatsApp group. The control group will receive the usual care and a pain management pamphlet. Data will be collected at baseline, and at the eighth-week and sixteenth-week follow-up session. The outcome measurements will include pain intensity, pain self-efficacy, perceived quality of life, depression, anxiety, and stress levels. Data on the caregiver burden will be collected from the informal caregivers. Because of the COVID-19 pandemic, all social activities have been suspended. In the near future, as the pandemic subsides, the dyadic pain management program will be launched to benefit community-dwelling older adults and informal caregivers and to reduce their pain and the care burden, respectively.

## 1. Introduction

The prevalence of chronic non-cancer pain is as high as 37% among community-dwelling older adults [1,2]. Pain is associated with significant physical and psychosocial incapacities [1,2,3]. Older adults with pain are more depressed and anxious and have reduced social interaction compared to those without pain [1,2,3]. Pain in older adults tends to be constant in nature, moderate to severe in intensity, and years long in duration [3,4]. Due to the physical vulnerability and immobility caused by chronic pain, older adults have decreased self-care ability and are at a high risk of falls [3,4].

Pain is often inadequately managed [4,5]. Analgesics remain the primary approach to managing pain [4,5]. However, older adults worry about adverse drug reactions and accept chronic pain as part of aging [2,3,4]. Hence, non-pharmacological strategies for managing pain, including pain education programs, exercise, massage, relaxation, and listening to music, are becoming increasingly popular [4,5,6].

Ersek et al. developed a pain management program using pain education, drugs, and a variety of non-pharmacological techniques, and found significant reductions in pain and improvements in physical and psychological parameters among the experimental group of older adults [7,8]. Drawing on their work, Tse et al. [9] implemented a pain management program that involved recruiting and training older adults to serve as peer volunteers in leading a pain management program for older adults living in nursing homes. After completing the program, the older adults were happier and reported less pain.

However, our peer-led pain management model may not benefit community-dwelling older adults with chronic pain, who require constant care from family members and caregivers [10]. In Hong Kong, more than 90% of older adults were found to be living in domestic households; of those, 25.2% were living only with their spouse, 29.0% were living with a spouse and children, and 19.5% were living only with their children [11]. That means that older adults are mainly being cared for by informal caregivers. An informal caregiver is a family member or close friend who has taken responsibility for the physical and emotional needs of a person who cannot entirely care for himself or herself because of advanced age, illness, dementia, or disability without an income [11].

Informal caregivers of older adults with chronic pain have a wide range of responsibilities that normally include helping the elderly in activities of daily living, reminding them to take their medications and to do exercises to relieve pain symptoms, taking them to the doctor when necessary, communicating with them, providing emotional support, and encouraging them to engage in social activities [12]. Caring responsibilities include providing help with daily activities and exercises to relieve pain symptoms and communicating with the older adults and providing them with emotional support [10,13]. Family members and carers have stated that it can be difficult to communicate with older adults with chronic non-cancer pain or to encourage them to participate in various non-pharmacological strategies for managing pain [8,9].

The majority of existing services focus on offering pain management education and programs to older adults/clients only, instead of to both older adults and their caregivers. Family members are important sources of interpersonal influence that can increase or decrease an individual’s commitment to engaging in health-promoting behavior [13,14]. Therefore, pain management programs should pair an older adult with his/her caregiver as a “dyad”.

Notably, the Health Promotion Model (HPM) describes the multidimensional nature of persons interacting with their interpersonal and physical environments in connection with the issue of health [13,14]. Utilizing the HPM, interventions involving a certain type of social support, such as a “dyadic” system, have a greater potential to increase the participation of older adults, encourage greater adherence to health-promoting activities, and result in a longer term of commitment and higher level of enjoyment [13,14].

A dyadic intervention could encourage patients to constantly take part in the intervention and enable their caregivers to be included in the same intervention. Dyadic interventions have been examined for clients with depression and dementia, yet, to the best of our knowledge, only two studies have used patient/caregiver dyads in a pain management intervention [15,16]. Keefe et al.’s [15] study targeted adults (mean age of 57) with osteoarthritic knee pain. Abbasi et al.’s [16] study targeted adult patients (aged 24–67 years) with chronic low back pain. Both studies involved pain-coping skills and exercise training and demonstrated improvements in pain intensity and psychological distress.

However, both studies were applied to those with osteoarthritic knee pain [15] or chronic low back pain [16]. In both studies, no prior power analysis had been conducted to estimate the sample size, putting their validity in doubt. Lastly, Abbasi’s study involved a multi-disciplinary team and intensive support from clinical psychologists, which could mean that the intervention might not be an affordable solution for patients with pain. More evidence is needed to determine whether the findings are generalizable to patients with other types of pain. It is for this reason that the present study is proposed.

## 2. Materials and Methods

### Aim and Objectives

To evaluate the effectiveness of a dyadic pain management program (DPM) in reducing pain and psychological health symptoms and improving pain self-efficacy, quality of life, and physical function in older adults when compared with a control population that received the usual care.

Primary objective:

To evaluate the effectiveness of a DPM in reducing pain scores.

Secondary objectives:

To evaluate the effectiveness of a DPM in reducing pain interference and psychological health symptoms (including levels of depression, anxiety, and stress), and enhancing pain self-efficacy and quality of life.

To explore the perspectives and experiences of informal caregivers and older adults on participating in the DPM.

## 3. Design and Setting of the Study

A cluster randomized controlled trial (RCT) will be used. It is a superior trial. Our study will be conducted in Neighborhood Elderly Centers (NECs) subsidized/run by the Social Welfare Department of Hong Kong. NECs offer a comprehensive range of community support services at the neighborhood level to enable older adults to remain in the community; lead a healthy, respectable, and dignified life; and contribute to society.

The target groups for NECs are adults aged 60 or above who live in the locality, carers, and the community at large. The scope of an NEC’s services include: providing health education, educational and developmental activities, information on community resources and referral services, volunteer development programs, carer support services, educational and support programes on dementia, counselling services, outreach and networking services, social and recreational activities, meal services, drop-in services, and so on. There are 169 NECs throughout the 18 districts in Hong Kong that are highly accessible to older adults in the community [17].

We chose NECs for collaboration because the major scope of their services is health promotion and carer support services, and because their convenient location in residential areas means that they are accessible to potential participants. The purpose of our research is in line with that of the NECs, which is to enable community-dwelling senior citizens to lead healthy and purposeful lives. Letters will be sent to all 169 NECs, inviting them to join the study. Those interested in participating will be randomized into the experimental or control group according to a computer-generated list. The unit of randomization is the NEC. The randomization will take place at the beginning of the study, and each NEC will be randomized into either an experimental group or a control group. This will prevent any possible contamination effect.

Allocation concealment, blinding, and the control arm: a statistician independent of the study team will use a random numbers table to make the assignments (1 = experimental DPM; 2 = control). The experimental group will receive the DPM and the control group will receive the usual care and a pain management pamphlet.

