## 7. Data Collection and Outcome Measures

A 36-month timeline is essential to recruit the required sample. Data collection will be carried out simultaneously in multiple sites.

Data will be collected at three time points: At baseline (T0), week 8 (T1), and week 16 (T2), using standardized methods and questionnaires, with a follow-up assessment (T2) to determine whether the observed benefits can be sustained over a longer period of time.

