## Figures and Tables

**Table 1 ijerph-19-12186-t001:** Schedule of enrolment, interventions, and assessments of DPM.

	Study Period				
	Enrolment	Allocation	Post-Allocation		
Timepoint	*Pre-Randomization*	*T0*	*Baseline (T0)*	*Week 8 (T1)*	*Week 16 (T2)*
ENROLMENT:					
Eligibility screen	X				
Informed consent	X				
Allocation		X			
INTERVENTIONS:					
*[Experimental Group: Dyadic pain management program]*					
*[Control group]*					
ASSESSMENTS:					
*[Pain intensity]*			X	X	X
*[Pain self-efficacy]*			X	X	X
*[Perceived quality of life]*			X	X	X
*[Psychological health: Depression, anxiety, stress]*			X	X	X
*[Caregiver Burden Inventory]*			X	X	X
*[Field evaluations]*			X	X	
*[Knowledge and skills acquired in managing pain situations for older adults]*			X	X	X
*[Semi-structured interviews for older adults and their caregivers]*				X	

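### Section 3 and Table 1 disagree on whether dyads enrol before or after their centre is randomised, and both leave the baseline pain score after allocation

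*Protocol article*

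**What the plan says.** Section 3 makes the centre the unit: "The unit of randomization is the NEC". All 169 NECs are invited by letter, and then: "Those interested in participating will be randomized into the experimental or control group according to a computer-generated list". On timing it says: "The randomization will take place at the beginning of the study". No dyad-level step is placed before this. On concealment, the same section states that "a statistician independent of the study team will use a random numbers table to make the assignments".

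Section 7 adds: "A 36-month timeline is essential to recruit the required sample", with data collection running at several sites at once.

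Table 1 gives the order by column. Eligibility screen and informed consent are marked under "Pre-Randomization". Allocation follows, in a column labelled T0. The baseline assessments, including pain intensity, are marked in a further column, also labelled T0, which stands under "Post-Allocation".

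Section 5 sets one list of entry criteria for older adults and one for caregivers, with no variant for control NECs. Both members of the dyad must be willing to join the dyadic pain management program (DPM), and the caregiver must be able to come to every centre session.

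**The concern.** In a cluster trial, concealing the sequence at centre level does not protect the selection of individuals within a centre. If the centre's arm is known when dyads are approached, those who agree to an eight-week exercise and education programme may differ from those who agree to usual care and a pamphlet. Criteria worded around the DPM are also hard to apply in the same way at a centre where no DPM will be offered.

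The baseline raises a separate issue. The primary outcome is pain intensity from a questionnaire (Section 7.1), and Section 8 compares outcomes across T0, T1 and T2. A T0 score given after the arm is known can be coloured by that knowledge, and T0 is the reference against which later scores are read.

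**Working it through.** The point concerns the order of events, so the check sets the statements side by side. The plan gives no figure to reproduce.

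**Order of steps**

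| Step | Section 3 with Section 7 | Table 1 |
|---|---|---|
| Dyad screening and consent | After randomisation, by implication: NECs are randomised at the start and recruitment takes 36 months | Before allocation |
| Allocation | Start of the study, per NEC | After consent |
| Baseline (T0) pain score | After randomisation, since it follows enrolment | After allocation |

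The screening in Table 1 is most naturally read as screening of people, because Section 5 gives criteria for older adults and caregivers and none for NECs. The first row therefore conflicts. The last row agrees, and it is the unfavourable order in both columns.

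**Can the size be derived?** No. The documents give neither a shift caused by knowledge of the arm nor a baseline-to-follow-up correlation. The following is purely illustrative. Inputs from Section 4: SD 2.1, planned difference 1.6, 75 dyads per arm, 20% drop-out, so 75 × 0.8 = 60 per arm. The design effect, 1 + (7 − 1) × 0.001 = 1.006, is ignored. Assumptions not in the documents: correlation ρ = 0.5, equal SDs at both times, and a baseline shift of 0.5 to 1.0 points.

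- *Recruitment shifts true baseline pain by δ.* The bias at week 8 depends on how T0 is used:
  - Unadjusted week-8 difference: ρδ = 0.25 to 0.5 points, or 0.25/1.6 = 16% to 0.5/1.6 = 31% of the planned difference.
  - Change from baseline: (ρ − 1)δ = −0.25 to −0.5.
  - Conditioning on T0: ρδ − ρδ = 0, but only if selection acts through baseline pain alone. Selection on motivation would remain.
- *Arm-aware reporting shifts only the recorded T0 by b.*
  - Unadjusted week-8 difference: 0.
  - Change from baseline: −b = −0.5 to −1.0.
  - Conditioning on T0: −ρb = −0.25 to −0.5.

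For the unadjusted week-8 comparison only, SE = 2.1 × √(2/60) = 0.383. A bias of 0.25 is 0.65 SE and gives a two-sided rejection rate of 10% at nominal 5%. A bias of 0.5 is 1.30 SE and gives 26%.

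These percentages do not describe the planned multilevel regression or generalized estimating equation (GEE) using T0, T1 and T2. The lists show that both sign and size depend on the mechanism and on how T0 enters the model.

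**The case against.** A reader might infer that dyads are in fact recruited after their NEC's arm is known, and that a false-positive rate of 10% to 26% follows. The document supports neither.

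- Table 1 puts screening and consent before randomisation, and nothing in the article says when centre staff, the research assistant or dyads learn the arm. That they would know is an inference from two visibly different arms.
- The 36 months cover the whole sample. About 7 dyads are expected per NEC (Section 4) and 6–7 per DPM group (Section 6), which would fit one short intake per centre in Table 1's order. The long period points to late recruitment only if Section 3's single early randomisation governs.
- Section 5 applies the same DPM-related criteria in both arms, which narrows the scope for different kinds of dyad to enter. It does not remove it, since those criteria may be applied differently where the arm is known.
- The illustrated error rates rest on assumed shifts and on a comparison the plan does not propose.
- A condensed article may leave masking of recruiters to the full protocol, so its absence here carries no weight.
- Both the Allocation and the Baseline columns carry the label T0, so the two may be meant as one visit.

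All of this limits the claim of bias. It does not reconcile Section 3 with Table 1, and it does not move the baseline ahead of allocation. A shared T0 label still leaves the order within that visit open, and the column heading places the assessments afterwards.

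**Conclusion.** The point holds as an inconsistency with conditional consequences. Section 3, read with Section 7, implies enrolment after the NEC is allocated; Table 1 states enrolment before it. If Section 3 is followed, recruitment and baseline are both exposed, and the DPM-specific entry criteria may operate differently in control NECs. If Table 1 is followed, recruitment is largely protected and only the post-allocation, self-reported baseline is exposed.

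The risk rests on the arms being distinguishable and on the arm possibly being known at recruitment or baseline. Bias is not established, and its size cannot be derived from the document. Reconciling the order must still be done before recruitment, because selection on unmeasured motivation cannot be repaired by analysis.

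**What to change.** State one order in Section 3 and Table 1. At each NEC, complete screening, consent and T0 questionnaires for that centre's dyads; only then does the independent statistician release that NEC's allocation. In Table 1, move the Baseline column ahead of Allocation and reserve the label T0 for the baseline assessment. In Section 3, replace the statement about randomising at the start of the study with this centre-by-centre release.

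If this is not feasible at some centres, say that recruiters and baseline assessors there are kept unaware of the arm, and report the numbers approached, eligible and consenting by arm and NEC.

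The cost is a change of wording, release of allocations one NEC at a time, and a short scheduling wait before each group starts. Each group of 6–7 dyads has to be assembled before its first session in any case, and Section 12 says that NECs were still being contacted when the article was written.

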## 5. Inclusion and Exclusion Criteria

Older adults/Participants: Inclusion criteria.

Aged 60 or above and being cared for mainly by an informal caregiver [11], with both the older adult and carer willing to participate in the DPM together.Scored > 6 in the Abbreviated Mental Test; a cut-off point of 6 is valid for differentiating between normal and abnormal cognitive functions in geriatric clients [10].Can understand Cantonese.Has a history of non-cancer pain in the past 6 months [20].Has a pain score of at least 2 on the Numeric Rating Scale (0–11 numeric scale) [21].Able to take part in light exercise and stretching.One member of the dyad owns a smartphone and can access the Internet.

Older adults/Participants: Exclusion criteria.

Has a serious organic disease or malignant tumor.Has a mental disorder diagnosed by neurologists or psychiatrists.Will have further medical/surgical treatment in two months.Experienced drug addiction [22].

Informal Caregivers: Inclusion criteria.

Aged 18 or above.Acting as an informal caregiver [11] for the participating older adult.Scored > 6 in the Abbreviated Mental Test; a cut-off point of 6 is valid for differentiating between normal and abnormal cognitive functions in geriatric clients [10].Can understand Chinese.Has a history of non-cancer pain in the past 6 months [20].Has a pain score of at least 2 on the Numeric Rating Scale (0–11 numeric scale) [21].Able to take part in light exercise and stretching.Owns a smartphone and can access the Internet.Able to attend whole sessions in the community activity center.

Informal Caregivers: Exclusion criteria.

Has a serious organic disease or malignant tumor.Has a history of cognitive or mental disorder diagnosed by neurologists or psychiatrists.Will have further medical/surgical treatment in two months or have joined another pain management program.Experienced drug addiction [20].

## 6. Intervention—Dyadic Pain Management Program (DPM)

The dyadic pain management program (DPM): The DPM is an 8-week group-based program. The DPM is comprised of 4 weeks of center-based, face-to-face activities and 4 weeks of digital-based activities delivered via a WhatsApp group. An 80% participation rate in the face-to-face activities will be regarded as completion of the DPM [9]. Timely make-up sessions will be arranged for those unable to attend the scheduled session. The experience from our pilot study indicates that there will be around 6–7 dyads in each DPM [18].

With regard to the face-to-face part, the DPM will start with 20–30 min of physical exercise supervised by the research assistant, followed by 20 min of pain management education, including information on the impacts of pain, the use of drug and non-drug strategies for pain management, and demonstrations and return demonstrations of various non-drug pain management techniques. Communication skills regarding the practice of various pain management techniques by the participants and their caregivers will be taught in the face-to-face session, and the participants will be encouraged to practice various pain relief methods at home. At the end of the session, the caregiver and research assistant will help the older adults to make portfolio entries on the activities of the day, to help them recall the various pain relief methods learned in each class [9].

For the home-based part, an exercise book will be given to each dyad to guide them in performing exercises at home. The recommendation is that they perform 30 min of exercise, three times a week, at home, but the more frequently, the better. The research assistant will show them how to use this exercise book in week 1 of the face-to-face sessions. The exercise book contains detailed images of each step in the exercises, which are the same exercises as those performed by the exercise dyads in the community center. This book will be given to each dyad to ensure that the participants know how to perform the exercises at home. The exercise book includes information on the whole exercise process: warming up, breathing, stretching, strength exercises, balance, and relaxation exercises. Reminders to practice and to record the completion rate will be sent via WhatsApp.

The use of a WhatsApp group (digital-based activities): All participants will join a WhatsApp group to receive teaching materials and videos of the physical exercises learned in class, for practice at home. Each dyad will be encouraged and reminded to practice the 30 min exercises together, three times per week, at home, and make entries in the WhatsApp group; and also to record their use of various types of non-pharmacological methods to relieve pain and their perception of the effectiveness of those methods. The team will produce a CD with video clips of the exercise for the dyads if the exercise video clips are too large to download from the WhatsApp group.

Protocols that govern the implementation of the planned measures and that act as a quality assurance mechanism.

